### Safety endpoints

Safety endpoints comprise vital status (mortality 90 days after randomization independent of ICU and hospital discharge status, hospital mortality, ICU mortality and proportion of patients discharged alive from ICU within 8 days), hypoglycemia, serious adverse events and complications related to the mode of nutrition.

Survival up to 90 days after randomization in both treatment groups will be compared by Kaplan Meier survival plots. The impact of "late PN" versus "early PN" will be analyzed, with and without correction for age, BMI & NRS categories and type and severity of illness, by Cox proportional hazard analysis. Vital status up to 90 days predictably will be traceable for virtually all patients via the National Registry, loss to follow-up will likely not be present except for some patients who will have a residence outside the Belgian territory. In addition, we will record vital status at ICU and hospital discharge and 90 days after randomization, and will analyze differences with Chi-square testing. All analyses will be performed in the intention to treat population. Correction of such differences in ICU and hospital mortality for age, BMI & NRS categories and type and severity of illness, will be performed using a multivariable logistic regression analysis, on condition of the absence of co-linearity between risk factors. Frequencies and percentages for both study arms will be presented together with odds ratios and 95% confidence intervals. As the randomized study intervention only takes place during a time window up to the 8^th ^day in ICU, we also plan to analyze early lethality within this time window in the intention to treat population as part of the safety analysis.

As patients not receiving early PN may be considered at increased risk for hypoglycemia, we will report for both groups the number of patients experiencing hypoglycemia <40 mg/dl during the time window of the randomized intervention. Hypoglycemia resistant to parenteral glucose administration is considered as a SAE and the incidence during the time window of the randomized intervention will be reported for both groups. In addition, overall blood glucose control during the time window of the intervention will be compared using daily morning blood glucose as well as daily maximal and minimal blood glucose. More sophisticated glucose metrics will be analyzed (among others hyperglycemic index, hypoglycemic index en glycemic penalty index) but such metrics fall beyond the scope of this initial report. Also, requirement of insulin will be compared.

Safety issues also comprise the occurrence of feeding-mode related complications during the time window of the intervention. Therefore, occurrence of these complications (digestive intolerance, complicated insertion of feeding tubes, pneumothorax, hemothorax and subclavian or carotid artery puncture, occlusion or displacement of central venous catheters or gastric feeding tubes) will be reported for both treatment groups.

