##### "Late PN"

Patients randomized to the "late PN" group receive a volume of Glucose 5% that is required to obtain adequate hydration taking into account the volume of EN that is being delivered. If enteral feeding of at least 80% of the calculated calories is not possible after 7 days in ICU, PN is initiated on day 8.

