#### Data collection following recruitment

All medications received by the patients during ICU stay are registered. Every day the amount of kilocalories, lipids, proteins, carbohydrates delivered by either PN or EN are calculated from the PDMS in an automated manner and entered into the case report form (CRF). For calculation of the energy requirements, 50% of the gastric residual volume, which is being discarded by the bedside nurses, is considered to be EN calories not absorbed by the patient. Interruptions of EN delivery and predefined digestive intolerance are registered daily. Mechanical complications such as displacement or obstruction of the enteral feeding tube or the central venous catheters; and clinical complications such as pneumothorax, hemothorax and subclavian or carotid artery puncture are recorded daily. Number of ICU days with a central line in situ is also noted. In addition we record the need for and the number of days of mechanical ventilatory support, of mechanical and pharmacological hemodynamic support, of renal replacement therapies and placement of tracheostomy.

Blood samples (a subset of which are immediately stored on ice for future endocrinological measurements) are taken upon ICU admission and daily at 06:00 h until discharge from ICU or death. All whole blood glucose levels are measured on arterial blood using a blood gas analyzer on each ICU and are registered for later calculation of glucose metrics.

Analyses on blood and urine for the primary clinical analyses include routine chemistry, hematology, and markers of inflammation. Further metabolic, endocrine and inflammatory measurements planned on stored samples in the context of mechanistic analyses fall beyond the scope of this paper. In addition, for later mechanistic studies, a random selection of patients are prospectively and repeatedly screened for the presence of sludge or cholecystitis on ultrasonography.

All new infections of the lungs, the blood stream, the urinary tract and wounds are recorded by an infectious disease specialist. Bacteraemia is further classified by responsible pathogen and as catheter related blood stream infection versus other bacteraemia [33,34].

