**Figure 3 F3:**
[figure not shown]
**CONSORT flow diagram**.

To assess compliance with the study protocol, the amounts of PN and EN actually given in the two study groups during the intervention window of 8 days will be reported as absolute numbers and percentages of target calories.

Discrete variables will be summarized by frequencies and percentages. Continuous variables will be summarized by use of either mean or standard deviations (SD) or median and interquartile range as appropriate.

Baseline and outcome variables will be compared using Student's t-test, (exact) Chi-square test and Mann-Whitney-U test, as appropriate.

All outcomes will be analyzed in an uncorrected manner as well as jointly corrected for risk factors (type and severity of illness, age, BMI and NRS categories). Type of illness will comprise the diagnostic categories, as stratified and grouped per organ system, as well as the presence or absence of a history of cancer. As severity of illness score for this correction, APACHE II will be used. BMI will be categorized as <20, 20-<25, 25-<30, 30-<40 and ≥40 kg/m2. Applicable NRS categories for this study are 3, 4, 5, 6 and 7. In case certain categories would appear underrepresented, such patients will be assigned to the next category in rank or previous category if it is the last category that is underrepresented.

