d. Need for pharmacological or mechanical hemodynamic support during ICU stay, and duration of such need. In addition, time to final (alive) weaning from all pharmacological or mechanical hemodynamic support in ICU will be analyzed, with ICU non-survivors censored beyond the longest duration of pharmacological or mechanical hemodynamic support of the survivors and censoring time of patients still on such support at closing of the data file (90 days after last patient inclusion) over both treatment groups.

e. Need for a tracheostomy during ICU stay.

f. Occurrence of infections during ICU stay: Number of patients with new infections and types of infection as specified in the study protocol and the duration of any antibiotics therapy initiated after randomization for those patients requiring antibiotics.

g. Cholestasis and liver dysfunction: Proportion of patients during the time window of the intervention and during the whole ICU stay presenting with cholestasis, defined as total bilirubinemia above 3 mg/dl or an increase to 150% of baseline value of gamma-glutamyltransferase or alkaline phosphatase. An increase of alanine or aspartate transaminases higher than 3 times the upper limit of normal will be considered as a marker of liver cytolytic damage. Proportion of patients presenting with such liver cytolytic damage during the time window of the intervention and during the whole stay in ICU will be compared. More subtle changes in liver enzymes will be analyzed by comparing the distribution of the highest values and the time course of the daily measurements.

h. Inflammation: Effect of the intervention on inflammation will be analyzed by comparing the distribution of the highest value reached during ICU stay and changes from baseline to the highest value and by comparing time profiles of daily C-Reactive Protein values.

i. Distribution of 6 MWD at hospital discharge in both treatment groups will be compared, as well as the proportion of patients unable to perform the test due to clinical reasons.

j. Proportion of patients independent for all ADL functions in both groups will be compared at hospital discharge. Hospital non-survivors will be analyzed as fully dependent for all functions.

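### Feeding-mode complications and hypoglycemia are counted only to about day 8, when late PN may begin; a whole-ICU-stay count should stand beside the window count

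*Protocol article*

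**What the plan says.** All references are to the protocol article.

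- **Which endpoints are limited.** Safety endpoints: "Safety issues also comprise the occurrence of feeding-mode related complications during the time window of the intervention". The same section reports "the number of patients experiencing hypoglycemia <40 mg/dl during the time window of the randomized intervention". For hypoglycemia resistant to glucose, which is treated as an SAE, "the incidence during the time window of the randomized intervention will be reported for both groups". It states no longer count for any of the three.
- **How long the window is.** General rules of the statistical analyses reports nutrition given "during the intervention window of 8 days". Safety endpoints says that "the randomized study intervention only takes place during a time window up to the" 8th ICU day.
- **When PN starts.** In the early arm PN starts on the second morning (Early PN section). In the late arm: "If enteral feeding of at least 80% of the calculated calories is not possible after 7 days in ICU, PN is initiated on day 8".
- **How other outcomes are counted.** Item g of Secondary efficacy endpoints uses two horizons: "Proportion of patients during the time window of the intervention and during the whole ICU stay presenting with cholestasis". Infections run over the ICU stay. Mortality is analysed within the window, at ICU and hospital discharge, and at 90 days.
- **What is recorded.** Data collection following recruitment: "clinical complications such as pneumothorax, hemothorax and subclavian or carotid artery puncture are recorded daily". Tube and catheter displacement or obstruction and digestive intolerance are also logged daily, and all arterial blood glucose values are registered.

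**The concern.** The trial compares two strategies for starting PN. The late strategy is not a strategy without PN: it includes PN from day 8 for patients whose enteral feeding falls short. For the three endpoints above, counting stops at about the point where that part of the strategy begins.

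The Rationale section suggests that late PN may help by avoiding complications of early PN. The Discussion says that a neutral result would let clinicians withhold PN safely for the first week. Both statements need a distinction between events that are avoided and events that move to the second week. A count that ends at day 8 cannot make that distinction for the part of these events that PN itself causes.

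**Working it through.** **1. Possible PN days inside the window**

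Take the window as ICU days 1 to 8.

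- Early arm: PN from day 2, so days 2 to 8, which is 8 - 2 + 1 = 7 days.
- Late arm: PN from day 8 at the earliest, so 1 day, or 0 if the window is read as closing before day 8.

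These are maxima. Early-arm PN also stops when enteral intake is sufficient, and late-arm PN starts only if it is not.

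**2. Check of the plan's stay distribution**

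Inputs from Sample size calculation: log-normal ICU stay T, mean 8, SD 13, median 4 days, 2320 patients per arm.

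- From mean and SD: s² = ln(1 + 13²/8²) = ln(3.641) = 1.292, so s = 1.137. The median is 8/exp(s²/2) = 4.19, close to the stated 4.
- From mean and median: s = √(2 ln(8/4)) = 1.177. The SD is 8√(exp(s²) - 1) = 13.9, close to the stated 13.

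The three stated figures agree to rounding. Both versions are carried forward.

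**3. Patients still in ICU after day 8**

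P(T > 8) = 1 - Φ[ln(8/median)/s]

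- Mean/SD version: ln(8/4.19)/1.137 = 0.568, giving 0.285. Then 0.285 × 2320 ≈ 661 per arm.
- Mean/median version: ln(2)/1.177 = 0.589, giving 0.278. Then 0.278 × 2320 ≈ 645 per arm.

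**4. Share of ICU patient-days after day 8**

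The share is E[(T - 8)⁺]/E[T]. Because the cut equals the mean, this reduces to 2Φ(s/2) - 1.

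- Mean/SD version: 2Φ(0.568) - 1 = 0.430.
- Mean/median version: 2Φ(0.589) - 1 = 0.444.

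**5. Ceiling on late-arm PN starters**

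P(T > 7) is 0.326 or 0.317, which is 756 or 736 of 2320. At most this many late-arm patients could start PN on day 8. The share who would actually start is not given.

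**6. What cannot be calculated**

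The documents give no rate for any listed complication, no hypoglycemia rate and no late-arm PN uptake. Steps 3 and 4 therefore measure how much follow-up lies outside these endpoints, in both arms alike. They do not measure a bias.

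**7. Why a plain whole-stay count is not enough**

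ICU stay is the primary endpoint, and the plan is sized to detect a one-day change from 8 days. At an identical constant daily event rate, an arm averaging 7 days expects 7/8 = 87.5% as many events as an arm averaging 8. That is 12.5% fewer events from exposure time alone.

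**The case against.** The strongest reply is that the window is a legitimate choice. It is the same in both randomized arms, it has a stated reason (the randomized intervention ends there), and it drops early-arm events after day 8 as well. That stands: the window result is a valid comparison of early events.

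A reader might infer that PN complications are counted in the early arm and hardly ever in the late arm, so that the safety comparison is biased by construction. The documents do not support this:

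- **The listed events are not specific to PN.** They are digestive, feeding-tube and central-line events. Both arms follow one early EN protocol, and patients without an indication for a central line are excluded. Both arms are therefore at risk from the start. Only the part of these events attributable to PN is affected.
- **Hypoglycemia is included because of withheld PN.** The window covers that period in the late arm. What remains is narrower: the glucose target applies to both groups with no stated end at day 8, so later episodes go uncounted in either arm.
- **Insulin requirement** is to be compared with no window stated, so it does not belong to this point.
- **Later harm is partly covered.** Mortality runs to 90 days. New infections are counted over the ICU stay, and bacteraemia is classified as catheter-related or other. Cholestasis and liver damage are analysed over the whole ICU stay. Among SAEs, a window is stated only for resistant hypoglycemia.

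Cholestasis is a secondary efficacy endpoint, so its two horizons do not prove an inconsistency. They do show that the plan already uses this pairing. The endpoints that run longer also do not directly count later tube problems, digestive intolerance, non-infectious line complications or hypoglycemia below 40 mg/dl.

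**Conclusion.** The point holds in a limited form. The fault is that the window count is the only count stated for these three endpoints, not that it exists. It spans about 7 possible PN days against at most 1, and leaves out about 28% of patients' later stay and 43-44% of ICU patient-days. It can therefore describe early events, but cannot show whether PN-attributable events under late PN were avoided or postponed. The point is firmest for catheter, tube and digestive events and weaker for hypoglycemia.

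These shares rest on the plan's log-normal planning assumption, on a window closing at the end of day 8, and on equal stay in both arms. The direction and size of any effect on the results are unknown. It would be wrong to conclude that a lower window count under late PN must be an artefact. It would be equally wrong to treat the whole-stay count as the one correct answer, since it depends on a length of stay that treatment may change.

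**What to change.** In Safety endpoints, keep the window analysis and add a comparison over the whole ICU stay for feeding-mode complications, hypoglycemia below 40 mg/dl and resistant hypoglycemia, in the same two-horizon form as item g. Because ICU stay may differ by arm, give the whole-stay result also per ICU day, or as cumulative incidence with ICU discharge and death as competing events. Base statements on the relative safety of the two strategies on both horizons, not on the window alone.

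The cost is a change of wording and some extra table rows. No new data collection should be needed, provided that the daily recording continues to ICU discharge; the data collection section states no stop at day 8. The downside is that whole-stay counts depend on length of stay and must be read with that in mind.

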### Primary efficacy endpoint

The primary efficacy endpoint for this RCT is the time to discharge alive from ICU. As the time of ICU discharge to the regular ward may be affected by the availability of beds on the regular wards, which could induce bias, we a priori decided to analyze "time to discharge from ICU" as "time to ready for discharge from ICU". A patient is considered "ready for discharge" as soon as all clinical conditions for ICU discharge have been fulfilled (no longer in need for vital organ support and receiving at least 2/3 of the caloric requirements as oral feeds) or earlier when the patient is actually sent to a regular ward.

Time to discharge alive from ICU will be reported by Kaplan Meier plots, with ICU non-survivors censored beyond the longest ICU stay of survivors and censoring time of patients still in the ICU at closing of the datafile (90 days after last patient inclusion) over both treatment groups. The impact of "late PN" versus "early PN" will be analyzed, with and without correction for age, BMI & NRS categories and type and severity of illness, by Cox proportional hazard analysis. The distribution of the actual time to discharge from ICU will be reported for ICU-survivors and ICU-non-survivors separately. In view of the time window of the randomized intervention in ICU, also the proportion of patients staying beyond 8 days in ICU will be reported.

### Secondary efficacy endpoints

All analyses will be performed uncorrected as well as corrected for age, BMI & NRS categories type and severity of illness. Time to event analysis will be analyzed similarly as the primary endpoint. Proportion of patients requiring support of vital organ functions and distribution of duration of support will be analyzed by non-parametric or parametric testing depending on the normality of the distribution in the subgroup of patients for which support was needed. Proportions will be compared using chi-square testing. Results of repeated measurements will be analyzed using an appropriate model for longitudinal data.

a. Time to discharge alive from the hospital, with patients still in the hospital at closing of the data file censored at that time point; patients transferred to another hospital censored on the day of transfer; and non-survivors censored beyond the longest hospital stay of survivors and censoring time of patients still in the hospital at closing of the data file (90 days after last patient inclusion) over both treatment groups.

b. Time to final (alive) weaning from mechanical respiratory support with patients still on mechanical respiratory support at closing of the data file being censored at that time point and ICU non-survivors censored beyond the longest duration of mechanical respiratory support of the survivors and censoring time of patients still on mechanical respiratory support at closing of the data file (90 days after last patient inclusion) over both treatment groups.

c. Kidney failure: Proportion of patients in need for renal replacement therapy (RRT) during ICU stay; distribution of duration of RRT (for those patients requiring RRT); proportion of patients with a post-randomization diagnosis of new kidney injury/failure (defined by modified Risk, Injury, Failure, Loss, and End-stage Kidney (RIFLE) classification criteria as a plasma creatinine doubling or more during ICU stay) in both treatment groups.

d. Need for pharmacological or mechanical hemodynamic support during ICU stay, and duration of such need. In addition, time to final (alive) weaning from all pharmacological or mechanical hemodynamic support in ICU will be analyzed, with ICU non-survivors censored beyond the longest duration of pharmacological or mechanical hemodynamic support of the survivors and censoring time of patients still on such support at closing of the data file (90 days after last patient inclusion) over both treatment groups.

e. Need for a tracheostomy during ICU stay.

f. Occurrence of infections during ICU stay: Number of patients with new infections and types of infection as specified in the study protocol and the duration of any antibiotics therapy initiated after randomization for those patients requiring antibiotics.

g. Cholestasis and liver dysfunction: Proportion of patients during the time window of the intervention and during the whole ICU stay presenting with cholestasis, defined as total bilirubinemia above 3 mg/dl or an increase to 150% of baseline value of gamma-glutamyltransferase or alkaline phosphatase. An increase of alanine or aspartate transaminases higher than 3 times the upper limit of normal will be considered as a marker of liver cytolytic damage. Proportion of patients presenting with such liver cytolytic damage during the time window of the intervention and during the whole stay in ICU will be compared. More subtle changes in liver enzymes will be analyzed by comparing the distribution of the highest values and the time course of the daily measurements.

h. Inflammation: Effect of the intervention on inflammation will be analyzed by comparing the distribution of the highest value reached during ICU stay and changes from baseline to the highest value and by comparing time profiles of daily C-Reactive Protein values.

i. Distribution of 6 MWD at hospital discharge in both treatment groups will be compared, as well as the proportion of patients unable to perform the test due to clinical reasons.

j. Proportion of patients independent for all ADL functions in both groups will be compared at hospital discharge. Hospital non-survivors will be analyzed as fully dependent for all functions.

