### Randomization

The study has a prospective, randomized, controlled, parallel-group design. Consecutive patients are randomly assigned to one of the two treatment study groups, labeled "Early PN" or "Late PN", using sequentially numbered, sealed and opaque envelopes. Upon addition of the study site Jessa Hospitals, these envelopes were replaced by an identical digital system allowing central computerized randomization. Patients are stratified per study site according to 17 primary diagnostic categories on admission. The stratified groups were labeled as follows:

I Medical-ICU admissions: (a) respiratory; (b) cardiovascular; (c) renal; (d) hematological/oncological; (e) GI/hepatic; (f) metabolic; (g) neurological (h) other;

II Surgical-ICU admissions according to referral discipline (a) cardiac surgery (elective or urgent surgery) (b) complicated thoracic surgery; (c) complicated vascular surgery (d) complicated abdominal and pelvic surgery (e) complicated neurosurgery (f) trauma and burns (g) transplantation (h) neurological disease (i) other.

Randomization - in a one to one allocation ratio - was performed using permuted blocks of 10, information that remained unknown to bed-side physicians and nurses, responsible for patient recruitment and therapy assignment.

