A priori defined subgroup analyses will be performed for BMI and NRS subcategories. These subgroup analyses are based on the rationale that BMI has been reported to be associated with different risk of outcome in different types of ICU patients which may be due to different handling of nutritional substrates [36-38]. This risk appeared different for patients with overweight or obesity (BMI 25 to <40) versus all other BMI categories (undernourished and normal BMI [BMI <20 and BMI 20-<25] or morbid obesity [BMI ≥ 40]). Therefore BMI will be dichotomized as such to optimize the power of this subgroup analysis. Also patients at higher risk of malnutrition may respond differently to the feeding strategies. Therefore, in this subgroup analysis, NRS will be dichotomized separating the highest risk patients [NRS ≥ 5] from the moderate risk patients [NRS 3 and 4]. Another a priori defined subgroup analysis will be performed for patients admitted to ICU after emergency or elective cardiac surgery as compared with all other patients. The shorter time in ICU of this subgroup may result in the early PN group receiving predominantly extra glucose 20% infusion, without lipids and amino-acids, as compared with the glucose 5% in the late PN group, which may evoke a different response than the full week combined parenteral nutrition. As sepsis is known to aggravate the metabolic disturbances evoked by early PN, a priori subgroup analysis is planned for patients with and without sepsis upon admission. These a priori defined subgroup analyses will be performed for the primary and safety endpoints without correction for other variables. To test for interaction between the identified subgroups and the studied intervention, a multivariable analysis (logistic regression or proportional hazard analysis as appropriate) will be performed for each subgroup variable separately and with the subgroup variable, the intervention and their interaction in the model. The interaction will be tested at a significance level of 0.1.

The first clinical report will analyze the impact of the nutritional strategies on safety (among which mortality), primary and secondary efficacy endpoints.

For all endpoints, differences will be considered statistically significant whenever the p-value reaches 0.05 or lower without correction for multiple testing.

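### Time to hospital discharge censors living transfers but keeps deaths in the risk set at full weight, so the alive-discharge curve falls below the correct cumulative incidence estimate; the treatment effect is distorted only if transfer differs by arm

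*Protocol article*

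**What the plan says.** Item a of *Secondary efficacy endpoints* sets three rules for time to discharge alive from the hospital:

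- Still in hospital: "patients still in the hospital at closing of the data file censored at that time point".
- Transferred: "patients transferred to another hospital censored on the day of transfer".
- Died: "non-survivors censored beyond the longest hospital stay of survivors", and also beyond the censoring times of those still in hospital, taken over both arms.

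The same section says "Time to event analysis will be analyzed similarly as the primary endpoint". Under *Primary efficacy endpoint* that means Kaplan-Meier ("Time to discharge alive from ICU will be reported by Kaplan Meier plots") and a treatment effect estimated "by Cox proportional hazard analysis". No censoring weights and no alternative handling of transfers are stated. *General rules of the statistical analyses* adds that "differences will be considered statistically significant whenever the p-value reaches 0.05 or lower without correction for multiple testing".

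**The concern.** Censoring deaths after the last possible event is a recognised device. A patient who dies can never be discharged alive, so keeping that patient in every risk set turns one minus Kaplan-Meier into the cumulative incidence of alive discharge. It works when living patients leave the risk set only by being discharged, or by closure of the data file. Since the file closes 90 days after the last inclusion, closure censors nobody before day 90.

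Transfer breaks that condition. Living patients drop out on the day of transfer, while the dead are never weighted down for the transfers they would have been exposed to had they lived. The late risk set then holds too many deaths, and the estimated discharge hazard is too small.

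Two things are at stake. One is the curve itself. The other is the hazard ratio: if one arm has more transfers, its late risk set is more distorted and its discharge hazard looks lower, with no difference in discharge or death. *Rationale of the study* names a shorter hospital stay as a possible benefit of late PN, so this endpoint will be read closely.

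**Working it through.** **Inputs.** From the article: allocation "in a one to one allocation ratio", 2320 per arm, two-sided 5% level, 20% ICU mortality. Not in the article, hence assumed: transfer share, hospital mortality, hospital stay and transfer mechanism. The plan has no figure on this point to reproduce. Its sample size is not in dispute: 20% v 23% at 70% power gives [1.960·√(2·0.215·0.785) + 0.524·√(0.20·0.80 + 0.23·0.77)]² / 0.03² = 2314.2, so 2315 per arm against the stated 2320.

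**Step 1, the curve under uninformative transfer.** Let d, m and c be constant hazards of alive discharge, death and transfer, λ = d + m + c and u = e^(−λt). At time t a fraction u is alive in hospital and (m/λ)(1 − u) has died. The planned rule uses the hazard

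h(t) = d·u / [u + (m/λ)(1 − u)],

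which integrates to

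1 − F(t) = [m/λ + (1 − m/λ)u]^(d/(d+c)).

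With c = 0 this is F(t) = d/(d+m)·(1 − u), the correct cumulative incidence. So the death rule alone is sound.

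Assume 15% hospital mortality and a mean stay of 20 days: d = 0.0425, m = 0.0075.

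- Truth at day 90: 0.85·(1 − e^(−4.5)) = 84.1%.
- 10% transferred: λ = 0.0556, m/λ = 0.135, u = e^(−5) = 0.0067, exponent 0.884. F = 1 − 0.1408^0.884 = 82.3%.
- 20% transferred: λ = 0.0625, m/λ = 0.12, u = e^(−5.625) = 0.0036, exponent 0.773. F = 1 − 0.1232^0.773 = 80.2%.

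The shortfall is 1.8 and 3.9 points. Aalen-Johansen on the same simulated data returns 84.1% in both cases. A separate simulation with 22% mortality and about 19% transferred independently gave 73.0% planned, against 77.2% for both truth and Aalen-Johansen.

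Long-run alive discharge, planned rule, constant hazards:

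| Mortality | Truth | 5% transferred | 10% | 20% | 30% |
|---|---|---|---|---|---|
| 20% | 80.0% | 79.0% | 77.8% | 75.3% | 72.2% |
| 10% | 90.0% | 89.2% | 88.3% | 86.1% | 83.5% |

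The median moves by less than half a day; the bias sits in the tail.

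**Step 2, the hazard between arms.** Assume 20% mortality, mean stay 20 days (d = 0.04, m = 0.01), identical discharge and death in both arms, and 10% v 20% transferred.

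- Day 10: 0.04·0.5738/(0.5738 + 0.18·0.4262) = 0.0353 v 0.04·0.5353/(0.5353 + 0.16·0.4647) = 0.0351; ratio 0.995.
- Day 40: 0.04·0.1084/(0.1084 + 0.18·0.8916) = 0.0161 v 0.04·0.0821/(0.0821 + 0.16·0.9179) = 0.0143; ratio 0.89.

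The arms agree early and separate late, with no true effect.

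**Step 3, simulated null trials, 2320 per arm, planned Cox analysis.**

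| Transfer mechanism | Mortality | Transferred | HR | Significant |
|---|---|---|---|---|
| Independent of recovery | 20% | 10% v 10% | 1.00 | 4% |
| Independent | 20% | 10% v 13% | 0.99 | 6% |
| Independent | 10% | 10% v 15% | 0.99 | 7% |
| Independent | 20% | 10% v 15% | 0.98 | 9% |
| Independent | 20% | 10% v 20% | 0.96 | 19% |
| Faster-recovering patients transferred | 15% | 9% v 14% | 0.98 | 9% |
| Faster-recovering patients transferred | 15% | 9% v 19% | 0.95 | 31% |
| Every transfer at 0.6 of own stay | 22% | 20% v 25% of survivors | 0.95 | 26-31% |

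Further independent-transfer runs with a 5-point gap gave HR 0.98 and 7% and 11% significant. The last row pools repeated runs of 400 to 1000 trials, with log-normal stay (median 15 days, log-SD 0.8). At 400 trials the simulation error is √(0.26·0.74/400) = 2.2 points, so that spread is largely noise. Equal transfer gave 4-6% throughout.

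**The case against.** The strongest case against is about size and remedy, and much of it stands.

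- **Nothing that drives the size is in the article.** It gives no transfer rate and no sign that the arms would differ. *Blinding of treatment allocation* says ward physicians and nurses are blinded, which limits allocation-driven transfer. This stands: with equal transfer the test keeps its level.
- **A reader might take 26-31% as the false-positive rate of the planned rule.** The article does not support that. The figure needs both a 5-point gap and transfer tied closely to each patient's own recovery. That mechanism also drives much of its curve shortfall: with 20% of survivors transferred, the planned curve gives about 71%, Aalen-Johansen about 73.5% and truth 77%. Only about 2.5 of the 6 points come from the handling of deaths; the rest is assumed dependent censoring.
- **A reader might expect Fine-Gray to remove the problem.** In that same scenario the planned analysis gave HR 0.947 with 31% significant, Fine-Gray with pooled censoring weights 0.947 with 30%, and with arm-specific weights 0.961 with 18%. Weighting must be arm-specific, and even then it does not cure informative transfer.
- **A reader might infer that the curve always understates true discharge.** It lay at or below Aalen-Johansen in every scenario where both were computed. Against true discharge from any hospital it can be too high: by up to about 1 point at days 15-30 if transferred patients recover much more slowly, and by up to about 2.5 points at the end if their death hazard is 4-8 times higher.
- **A reader might infer that an arm leaving ICU sooner is penalised artificially.** Leaving ICU sooner would itself be a treatment effect, and the article says nothing about its effect on transfer.
- **The scope is narrow.** Transfer censoring is stated for item a alone. The primary endpoint, mortality and the weaning endpoints carry no such rule.

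None of this rescues the combination of rules. It is stated explicitly, so it is not a detail left to a fuller plan, and it gives a wrong curve even under the most favourable assumption about transfer.

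**Conclusion.** The point holds as an inconsistency in the estimator for one secondary endpoint. Kaplan-Meier and Cox with transfers censored and deaths held at full weight do not estimate the cumulative incidence of alive discharge. The curve lies below Aalen-Johansen even with uninformative transfer, by about 2 to 4 points at day 90 when 10-20% are transferred, assuming 15-22% hospital mortality.

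The between-arm consequence is conditional. It needs unequal transfer, and for a 5-point gap it ranges from slight (HR about 0.98, 7-11% significant) to material (HR about 0.95, 26-31%), depending on how closely transfer follows recovery. The article does not say which applies. The correction should be made, but nothing here questions the primary endpoint or the death rule taken alone.

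**What to change.** Amend item a before the data file is finalised:

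1. Report alive discharge by the Aalen-Johansen estimator, with death as a competing event and transfer as censoring.
2. Estimate the treatment effect, uncorrected and corrected, with a subdistribution (Fine-Gray) model whose censoring weights are estimated separately by arm.
3. Report the number and timing of transfers by arm.
4. Add a sensitivity analysis counting alive transfer as the end of study-hospital stay, labelled as a different estimand.
5. State that the weighting corrects the handling of deaths but not informative transfer, so an apparent effect on hospital stay will be read cautiously if transfer rates differ by arm.

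The conclusion should not depend on analyses 2 and 4 agreeing. They target different quantities, and counting transfer as discharge can itself create an effect: under independent transfer with unequal rates, a null simulation gave HR 1.06 with 44% of trials significant.

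The cost is revised wording and a little more analysis on a secondary endpoint. The planned analysis already needs the dates of transfer, discharge and death. Discharge from the receiving hospital is not stated to be collected (*Data conservation and processing* mentions only vital status at 90 days), so the fix does not rely on it.
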